**Methods/design:**

Patients will be randomized 2:1 to SABR or observation with minimization to balance assignment by primary intervention, prior hormonal therapy, and PSA doubling time. Progression after 6 months will be compared using Fisher’s exact test. Hazard ratios and Kaplan-Meier estimates of progression free survival (PFS), ADT free survival (ADT-FS), time to locoregional progression (TTLP) and time to distant progression (TTDP) will be calculated based on an intention-to-treat. Local control will be assessed using Response Evaluation Criteria in Solid Tumors (RECIST) 1.1 criteria. Withdrawal from the study prior to 6 months will be counted as progression. Adverse events will be summarized by type and grade. Quality of life pre- and post- SABR will be measured by Brief Pain Inventory.

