#### Secondary endpoints

To describe the toxicity of SBRT/SABR delivered for the population enrolled using Common Terminology Criteria for Adverse Events (CTCAE) version 4.0.To determine local control at 6-months after SABR in patients with oligometastatic disease.To assess progression free survival (PFS) and ADT-free survival (ADT-FS) after randomization defined as the time interval between the day of randomization and progression.To assess quality of life in the SBRT/SABR arm using the Brief Pain Inventory form [34].To estimate the proportion of ^18^F-DCFPyL-PET/MRI or –PET/CT positive sites that are positive for new or progressive metastatic disease by bone scan/CT at baseline and 6 months following SABR and vice versa.To enumerate CTCs using EPIC HD-CTC platforms at baseline and day 180 from randomization.To enumerate circulating tumor DNA (ctDNA) using Cancer Personalized Profiling by deep sequencing (CAPP-Seq) at baseline, day 90 and day 180 from randomization for control and SABR arms.To quantitatively sequence T-cell receptor (TCR) repertoires using peripheral blood monocytes and the ImmunoSEQ platform at baseline and day 90 from randomization.

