#### Inclusion criteria

Patient must have 1-3 asypmtomatic metastatic tumor(s) of the bone or soft tissue developed within the past 6-months that are ≤ 5.0 cm or < 250 cm^3.^
Patient must have had their primary tumor treated with surgery and/or radiation and salvage radiation to the prostate bed or pelvis is allowed.Histologic confirmation of malignancy (primary or metastatic tumor).Prostate specific antigen (PSA) ≥ 0.5 ng/mL but ≤ 50 ng/mL and Testosterone ≥ 125 ng/dL.PSA doubling time (PSADT) < 15 months. PSADT will be calculated using as many PSA values that are available from time of relapse (PSA > 0.2 ng/dL).Patient may have had prior systemic therapy and/or ADT associated with treatment of their primary prostate cancer. Patient may have had ADT associated with salvage radiation therapy.Patient must be ≥ 18 years of age, have the ability to understand, and the willingness to sign, a written informed consent document.Patient must have an Eastern Cooperative Oncology Group performance status ≤ 2.Patient must have normal organ and marrow function as defined as:Leukocytes >2,000/μL, absolute neutrophil count >1,000/μL, platelets >50,000/μL

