### Evaluation of randomization and blinding

This study will employ a randomized phase II design to determine the appropriateness of a subsequent phase III trial based on comparison of rate of progression at 6 months. An interactive web response system (IWRS) will be utilized to obtain the patient’s randomization assignment. Randomization will occur in a 2:1 fashion for SABR and observation arms, respectively. A minimization approach [35] will be applied to ensure balanced assignment to each treatment arm by: 1) Initial treatment with surgery vs. radiation therapy; 2) Prior hormonal therapy vs. no prior hormonal therapy; and 3) PSADT <6 mos vs. 6-14.9 mos. The on-study date for protocol entry will be the day that the study subject is randomized. Patients will be re-evaluated for radiographic response 6 months after randomization. Trial radiologists evaluating for treatment responses will be blinded to the treatment group and treatment specifics. The trial radiologists and the principal investigator will be unblinded only if a patient progresses at any time during the study.

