**Fig. 1 Fig1:**
[figure not shown]
ORIOLE Study Schema. Subjects who meet eligibility criteria and qualify for enrollment will be stratified and randomized as demonstrated

The following is a detailed outline, after randomization, involving each study arm:Observation Arm: Active Clinical Surveillance
Defined with 3 time points, involving the following:

Day 1Standard blood tests [complete blood count with differential (CBC w/Diff), lactate dehydrogenase (LDH), serum chemistry, and PSA evaluation]Research laboratory tests: CAPP-Seq, rectal swab, and Color Test

Day 90Physician examination, medical history, medication review, performance status, quality of life (QoL) and adverse event (AE) evaluationsStandard blood tests (CBC w/Diff, LDH, serum chemistry, testosterone, and PSA evaluation)Research blood tests: CAPP-Seq

Day 180Physician examination, medical history, medication review, performance status, QoL and AE evaluationsStandard blood tests (CBC w/Diff, LDH, serum chemistry, testosterone and PSA evaluation),Research blood tests: CAPP-SeqImaging: bone scan and CT/MRI
2.SABR Arm:
Defined with 3 time points, involving the following:Day 1Standard blood tests (CBC w/Diff, LDH, serum chemistry, and PSA evaluation)Research laboratory tests: EPIC HD-CTC, ImmunoSEQ, CAPP-Seq, rectal swab, and Color TestImaging: ^18^F-DCFPyL PET/CT or PET/MRI
Day 90Physician examination, medical history, medication review, performance status, QoL and AE evaluationsStandard blood tests (CBC w/Diff, LDH, serum chemistry, testosterone, and PSA evaluation)Research blood tests: ImmunoSEQ, CAPP-Seq
Day 180Physician examination, medical history, medication review, performance status, QoL and AE evaluationsStandard blood tests (CBC w/Diff, LDH, serum chemistry, testosterone, and PSA evaluation)Research blood tests: EPIC HD-CTC, CAPP-SeqImaging: Bone scan and ^8^F-DCFPyL PET/CT or PET/MRI
Research Imaging
^18^F-DCFPyL PET/CT or PET/MRI images will be evaluated and compared to bone scan. However, additional sites(s) of suspected metastatic disease detected using ^18^F-DCFPyL will not be considered for treatment by SABR or undergo further evaluation. The results of PSMA-targeted PET imaging will not be made available to the treating physicians until after the trial is completed and these results will not be made available to the patient.SBRT/SABR Planning and Dosage:

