Site-specific grade 4/5 toxicity will be monitored in the SABR arm. If it becomes evident that the proportion of grade 4/5 toxicity at specific sites convincingly exceeds 20%, the study will be halted for a safety consultation. Specifically, we will apply a Bayesian toxicity monitoring rule that suspends the enrollment for a posterior probability ≥ 75% of toxicity being larger than 20%. The monitoring rule uses Beta (0.5, 5.5) as prior distribution, meaning our prior guess of the proportion of toxicity is 8.3% with a 90% chance that this proportion is 0.04%-30.6%.

Follow-Up:Patients will be followed from Day 1 to Day 180.All AEs and serious adverse events (SAEs) are recorded on source documents. The investigator will follow up on all AEs and SAEs until the events have subsided, returned to baseline or, in case of permanent impairment, until the condition stabilizes.

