##### 2.4.2.2.Analysis of secondary objectives

For safety analysis, adverse events will be summarized by type and grade.Hazard rate estimates and 95% confidence intervals as well as Kaplan-Meier (KM) estimates will be calculated for PFS, ADT-FS, TTLP and TTDP. The median PFS, ADT-FS, TTLP and TTDP will be reported.Each metastatic lesion will be considered a target lesion and independently evaluated for response using RECIST 1.1 or bone scan evaluation criteria below. The lesion will be coded as locally controlled if it is considered stable radiographic disease or if there is evidence of a partial or complete response. Local control assessment will start at three months following randomization and continuous assessment will be pursued during the follow-up period. The proportion of locally controlled lesions will be estimated using generalized estimating equations.QoL will be assessed using the Brief Pain Inventory form. An overall score will be calculated pre-treatment and at the time of the 2^nd^ radiologic reassessment. The change in score will be evaluated by paired t-test.

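### Quality of life is tested only as a before-after change in SABR patients, although it is collected in both randomised arms, and the time point does not match the visit schedule

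*Protocol article*

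**What the plan says.** The Secondary endpoints section sets the objective: "To assess quality of life in the SBRT/SABR arm using the Brief Pain Inventory form". The abstract's Methods/design paragraph agrees: "Quality of life pre- and post- SABR will be measured by Brief Pain Inventory".

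Section 2.4.2.2 (Analysis of secondary objectives) gives the analysis: "An overall score will be calculated pre-treatment and at the time of the 2^nd^ radiologic reassessment", and then "The change in score will be evaluated by paired t-test". That section does not itself name an arm. The restriction to SABR comes from the objective and the abstract.

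The visit lists under Interventions put quality of life at Day 90 and Day 180 in the observation arm ("performance status, quality of life (QoL) and adverse event (AE" at Day 90) and at the same two visits in the SABR arm. Post-baseline imaging is listed once per arm, at Day 180. Evaluation of randomization and blinding says "Patients will be re-evaluated for radiographic response 6 months after randomization", and the follow-up text says "Patients will be followed from Day 1 to Day 180". Section 2.4.2.2, however, starts local control assessment three months after randomisation.

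The Background expects SABR to delay hormonal therapy, spare patients its side effects and so improve quality of life.

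**The concern.** The trial has a concurrent randomised control group that answers the quality-of-life questions at the same visits, but the stated test uses only the SABR arm. The expectation in the Background is comparative: quality of life should be better with SABR than without it. A change from before to after treatment combines any SABR effect with whatever would have happened over six months anyway.

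This matters because drift is plausible here. The sample-size section expects 40% of SABR patients to progress within six months even if the treatment works as hoped, against 80% under observation. SABR could therefore help while the SABR arm's own score stays flat or worsens. Conversely, an improvement in that arm need not be due to SABR.

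A second, smaller problem is that the end time point is tied to a radiologic visit that cannot be matched directly to the schedule.

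**Working it through.** **Time points, side by side**

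| Item | Observation | SABR |
|---|---|---|
| Quality of life, post-baseline | Days 90, 180 | Days 90, 180 |
| Imaging, post-baseline | Day 180 | Day 180 |
| Stated quality-of-life analysis | none | paired t-test |

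Counting only listed post-baseline scans, Day 180 is the first reassessment and there is no second. If a three-month scan is inferred from the local control sentence, or if baseline imaging is counted as the first, Day 180 becomes the second. The text does not say which is meant.

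**What the paired change estimates**

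Let τ be the mean change that would occur without SABR and δ the SABR effect.
- Mean change in the SABR arm: τ + δ.
- Mean change in the observation arm: τ.
- Difference between arms: δ.

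The paired t-test tests τ + δ = 0. Running it in each arm separately would still not test δ.

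**Illustration with δ = 0**

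The plan gives no power figure, SD or target effect for quality of life, so there is nothing to reproduce. Its 85% power refers to progression and is not at issue. Inputs are n = 36 SABR and 18 observation (Sample size and accrual) and an assumed two-sided 5% level. Effects are in SDs of the change score. The paired test has noncentrality τ × √36 = 6τ on 35 degrees of freedom:

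| τ (SD of change) | 6τ | Probability of p < 0.05 |
|---|---|---|
| 0.2 | 1.2 | 21% |
| 0.3 | 1.8 | 42% |
| 0.4 | 2.4 | 65% |
| 0.5 | 3.0 | 83% |

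A between-arm comparison holds 5% in every row, because τ cancels.

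**Precision of the between-arm contrast**

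These figures use 80% power, two-sided 5%, the normal approximation with 1.96 + 0.84 = 2.80, and complete data.
- Paired, n = 36: 2.80 / √36 = 0.47 SD of change. This is the detectable τ + δ, not δ.
- Between arms, unadjusted: 2.80 × √(1/36 + 1/18) = 2.80 × 0.2887 = 0.81 SD. With the t distribution, power is 78% at 0.80 SD and 81% at 0.83 SD, so the approximation is close.
- ANCOVA with baseline correlation r multiplies this by √(1 − r²). The correlation is not in the document. At r = 0.3: 0.81 × 0.954 = 0.77 SD. At r = 0.5: 0.81 × 0.866 = 0.70 SD. At r = 0.7: 0.81 × 0.714 = 0.58 SD.
- 95% CI half-width: 1.96 × 0.2887 = 0.57 SD unadjusted, and 0.57 × 0.866 = 0.49 SD at r = 0.5.

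On units: the paired figure is in SDs of change and the ANCOVA figures are in SDs of the score. The SD of change equals the SD of the score times √(2(1 − r)), so the two scales coincide at r = 0.5 and differ otherwise.

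**The case against.** The strongest defence is that the test fits the objective as written. The objective is to assess quality of life in SABR patients before and after treatment, a paired test does that, and section 2.4.2.2 does not say that the change will be read as an effect against observation. A descriptive single-arm objective is acceptable in a small phase II trial. This stands as far as it goes: the paired analysis does not contradict its own objective, and it can stay. It does not explain why control data collected at the same visits have no stated use while the Background anticipates a benefit from SABR.

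The defence also limits several stronger conclusions that a reader might draw.

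- *The endpoint visit does not exist.* The three-month start of local control assessment, or counting baseline imaging, makes Day 180 a natural reading, and quality of life is collected then. The problem is a label that does not match the schedule.
- *The pre-treatment score is not scheduled.* No quality-of-life item is listed at Day 1. The article's entry lists are visibly condensed, though: performance status and testosterone are eligibility criteria, yet neither appears in the work-up or at Day 1. Section 2.4.2.2 and the abstract both promise a pre-treatment score.
- *Pain scores start at the floor, and slower worsening would be reported as harm.* Eligibility says "Patient must have 1-3 asypmtomatic metastatic tumor(s", which makes little room for improvement plausible. The document gives no BPI data, does not exclude pain from other causes, and states no such reporting rule.
- *A between-arm BPI comparison would settle the Background's claim.* The BPI measures pain, whereas the anticipated benefit comes largely from avoiding side effects of hormonal therapy. The comparison tests that claim only in part.

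Finally, the contrast with 18 controls is imprecise, and self-report in a non-blinded trial can be biased even when the allocation is random. Both points stand.

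**Conclusion.** The concern holds in a limited form. The stated quality-of-life test cannot isolate a SABR effect, and the observation-arm data have no stated analysis. The 21% to 83% range shows the size of the problem under assumed common shifts of 0.2 to 0.5 SD. It is an illustration, not a prediction, because the document gives no BPI mean, SD or correlation. The end time point needs to be tied to a named visit.

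This is a secondary endpoint, so the change is advisable rather than critical. The between-arm result would detect only about 0.8 SD unadjusted, or about 0.7 SD at an assumed correlation of 0.5, with all 54 patients contributing and less sensitivity after withdrawals. The paired test's 0.47 SD is no advantage, since it refers to a different quantity. The documents do not support saying that the paired analysis is invalid for its descriptive purpose, or that baseline BPI is not collected.

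**What to change.** 1. Add a between-arm comparison of the BPI score at Day 180 in all randomised patients, by ANCOVA on the pre-treatment score with a 95% CI. Treat Day 90 as supportive.
2. Keep the SABR within-arm change, labelled as descriptive.
3. Replace the reference to a second radiologic reassessment with Day 180, and reconcile the three-month start of local control assessment with the imaging schedule.
4. Make sure the pre-treatment BPI is taken in both arms. If it is not available for controls, compare Day 180 scores unadjusted.
5. Present the result as an estimate, noting the unblinded self-report and that the BPI covers pain rather than side effects of hormonal therapy.

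The cost is small: analysis wording and, if it is not already done, one short questionnaire before treatment in each arm. The post-baseline quality-of-life assessments are already scheduled. The price is a wide interval, about ±0.57 SD unadjusted or ±0.49 SD at an assumed correlation of 0.5.

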#### Response criteria

Evaluation of Target Lesions and PSA Response

Complete Response (CR): Disappearance of all target lesions and PSA below baseline
Partial Response (PR): At least a 30% decrease in the sum of the longest diameter (LD) of target lesions, taking as reference the baseline sum OR at least 1/3 of lesions are stable or resolved by bone scan AND PSA below baseline
Progressive Disease (PD): At least a 20% increase in the sum of the LD of target lesions, taking as reference the smallest sum LD recorded since treatment initiation OR the appearance of >1 new lesion(s) by bone scan OR PSA ≥25% above nadir or > 50 ng/ml.
Stable Disease (SD): Neither sufficient shrinkage to qualify for PR nor sufficient increase to qualify for PD, taking as reference the smallest sum LD since treatment initiation OR PSA > baseline but not ≥25% above nadir and <50 ng/ml.
Complete Response (CR): Disappearance of all target lesions and PSA below baseline
Partial Response (PR): At least a 30% decrease in the sum of the longest diameter (LD) of target lesions, taking as reference the baseline sum OR at least 1/3 of lesions are stable or resolved by bone scan AND PSA below baseline
Progressive Disease (PD): At least a 20% increase in the sum of the LD of target lesions, taking as reference the smallest sum LD recorded since treatment initiation OR the appearance of >1 new lesion(s) by bone scan OR PSA ≥25% above nadir or > 50 ng/ml.
Stable Disease (SD): Neither sufficient shrinkage to qualify for PR nor sufficient increase to qualify for PD, taking as reference the smallest sum LD since treatment initiation OR PSA > baseline but not ≥25% above nadir and <50 ng/ml.

b.Evaluation of Best Overall Response: The best overall response is the best response recorded between treatment initiation and disease progression/recurrencec.Duration of Response: Response will be defined as evidence of CR, PR, or stable disease.

Duration of CR or PR: The duration of CR or PR will be recorded from the date criteria for CR or PR are first met until the first date current or progressive disease is objectively documented (taking as reference for progressive disease the smallest measurements recorded since treatment initiation).
Duration of Stable Disease: Stable disease will be recorded until the criteria for progression are met, taking as reference the smallest measurements recorded since the treatment started.

## Discussion

The standard treatment options for metastatic hormone sensitive prostate cancer have remained unchanged for many years involving principally hormonal therapy. However, hormonal therapy can have troublesome side effects and any effort to delay the start of hormonal therapy would be an advantage to the patient. Radiation treatment was historically not given at high enough doses to metastases to provide durable local control. SABR is highly targeted radiation, delivered in a dose-intensive fashion in 1 to 5 fractions, which has been shown to be very effective on bone and soft tissue metastases. This phase II randomized study will compare SABR to observation with respect to progression of disease, freedom from hormonal therapy, and other relevant clinical endpoints. Simultaneously, a unique perspective on the impact of SABR on the biology of the oligometastatic state will be obtained through correlation of clinical response with measures of tumor burden, hematologic dynamics of metastasis, and immunologic response. Finally, the pursuit of patient-centered, personalized approaches to treatment will be furthered through investigation of targeted imaging and genomic susceptibility characterization.

## Abbreviations

ADL: Activities of daily living
ADT: Androgen deprivation therapy
AE: Adverse event
BID: Twice daily
BSA: Body surface area
CBC: Complete blood count
CI: Confidence interval
CMAX: Maximum concentration of drug
CNS: Central nervous system
CR: Complete response
CRF: Case report/Record form
CRPC: Castration-Resistant Prostate Cancer
CTC: Circulating Tumor Cell
CTCAE: Common Terminology Criteria for Adverse Events
DLT: Dose Limiting Toxicity
DSMB: Data Safety Monitoring Board
ECG: Electrocardiogram
GI: Gastrointestinal
Hgb: Hemoglobin
HIV: Human Immunodeficiency Virus
HPF: High-power field
HTN: Hypertensions
IRB: Institutional Review Board
IV: Intravenous
LLN: Lower limit of normal
MTD: Maximum tolerated dose
OS: Overall survival
PD: Progressive diseased
PFS: Progression free survival
PLT: Platelet
PR: Partial response
PSADT: PSA Doubling Time
QD: Once daily
RECIST: Response evaluation criteria in solid tumors
RR: Response rate
SABR: Stereotactic ablative radiation therapy
SAE: Serious adverse event
SBRT: Stereotactic body radiation therapy
SD: Stable disease
TTP: Time to progression
ULN: Upper limit of normal
UNK: Unknown
WBC: White blood cell
